**Methods:**

MOST+ will be embedded within eheadspace, an Australian youth e-mental health service, and will be evaluated via an uncontrolled single-group study. Approximately 250 help-seeking young people (16-25 years) will be progressively recruited to the intervention from the eheadspace home page over the first 4 weeks of an 8-week intervention period. All participants will have access to evidence-based therapeutic content and integrated Web chat counseling. Additional access to moderated peer-to-peer social networking will be granted to individuals for whom it is deemed safe and appropriate, through a three-tiered screening process. Participants will be enrolled in the MOST+ intervention for 1 week, with the option to renew their enrollment across the duration of the pilot. Participants will complete a survey at enrollment to assess psychological well-being and other mental health outcomes. Additional assessment will occur following account deactivation (ie, after participant has opted not to renew their enrollment, or at trial conclusion) and will include an online survey and telephone interview assessing psychological well-being and experience of using MOST+.

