### Participants

Inclusion criteria for participants will reflect the real world clinical characteristics of young people accessing e-mental health support, that is, (1) Help-seeking young people with concerns about their own mental health, (2) Age of 16 to 25 years inclusive, and (3) Ability to give informed consent and comply with study procedures. By the age of 16 years, young people in Australia are considered able to make independent decisions regarding their health care [28]. An age range of 16 to 25 years reflects the agency of young people to make their own health service choices, while ensuring the age appropriateness of the therapeutic material and social networking features of the MOST+ platform. Existing eheadspace clients meeting these criteria will be eligible to use the MOST+ intervention.

Consistent with current eheadspace practice, participants will not be excluded from the study on the basis of clinical characteristics. However, the following exclusions will apply for access to the social networking component of the intervention: (1) acute risk of self-harm requiring urgent intervention (ie, suicidal ideation with a current plan and intent to enact this plan) indicated by a young person in Web chat or by endorsing screening questions 7 and 8 in the registration survey; (2) an eheadspace clinician, in consultation with a supervisor, deems participation in the MOST+ social network likely to interfere with appropriate clinical management of mental health symptoms (eg, psychosis) or increase risk of harm to self or others (see Figure 1); and (3) inability to confirm age and conduct induction via research assistant (RA) telephone contact.

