#### Duration of Access

Regardless of level of access, all participants will be enrolled in the MOST+ intervention for 1 week, with the option to extend their enrollment on a weekly basis across the study intervention period. Thus, participants’ period of enrollment in the intervention will range from a minimum of 1 week to a maximum of 8 weeks. Participants will be able to reactivate an expired account at any time during the study intervention period, and this will be treated as a second episode of care. Following the conclusion of the pilot study, participants will be redirected to eheadspace if they attempt to log into the MOST+ platform. See Figure 3 for examples of participants’ possible enrollment time lines, with each colored line representing a different potential time line over the duration of the pilot.

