### Outcomes

The primary outcome variables will be intervention feasibility, acceptability, and safety. Assessment of intervention feasibility will involve reviewing a log of participants' access to, and usage of, the MOST+ platform. Access data will include the number of participants recruited and retained through the study, participants’ level of access, reasons for maintained partial access following initial intervention enrollment, and details of any full or partial withdrawals from the intervention. Usage data will include the number of log-ins, steps completed, and contributions to Talk It Out and The Café. This is the first study piloting an intervention of this nature and scale for help-seeking young people and, as such, registration and usage rates are difficult to predict. For this reason, an *a priori* criterion for the number of active users that would indicate study feasibility has not been defined.

Acceptability will be assessed at follow-up using specially designed questions administered within a semistructured feedback interview. Acceptability will be considered achieved if (1) Participants provide ratings of the MOST+ platform averaging above three out of five across feedback questions regarding ease of use, relevancy, helpfulness, and overall experience; (2) At least 60% of participants report that the MOST+ intervention provided timely, relevant, and helpful support at semistructured follow-up interview; and (3) At least 80% of respondents would recommend MOST+ to other young people experiencing difficulties.

The pilot will be considered to indicate safety of the MOST+ intervention if (1) At least 90% of participants report the online intervention to be safe via semistructured feedback interview at follow-up; (2) None of the participants experience a serious adverse event as a result of their engagement with the system during their intervention period (ie, none of the participants experience a significant deterioration in mental health or self-harm in response to intervention content, as reported by the participant or determined by treating health care professionals); and (3) There are no unlawful entries into the MOST+ system detected by study programmer during the 8-week pilot.

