### Data Collection and Management

All participants will receive one AUS $30 voucher as reimbursement for their time in completing registration and another for completing follow-up. Follow-up assessment will occur approximately 4 days after initial account deactivation (ie, 4 days after a user has opted not to renew their account for an additional week). For those participants who maintain active enrollment across the intervention period, follow-up will occur as soon as possible following conclusion of the pilot. The exact duration of follow-up cannot be estimated as the number of participants enrolled in MOST+ will not be capped. To minimize attrition, participants will receive a short service message notification that their online follow-up survey is due and will be able to complete survey items either online or via telephone. Participants who do not complete the follow-up survey will be reminded via phone call by an RA. Both baseline and follow-up assessments will be designed to minimize participant burden, while ensuring that requirements for the eheadspace Minimum Data Set (MDS; ie, routine data about each occasion of service) are met.

The MOST+ system and data generated through participants’ use of the online platform will be hosted on a secure University of Melbourne Web server. Data collected via online surveys and telephone interviews will be entered electronically and also centrally stored on a University of Melbourne Web server. At the conclusion of the study, this data will be exported and stored securely in a password protected file on the server at Orygen. In addition, data collected as part of eheadspace MDS requirements will be provided to headspace at the conclusion of the study. For each MOST+ account, clinical content collected via Web chat and surveys will be copied into an eheadspace account to ensure continuity of care should the participant continue using eheadspace services post trial.

All of the PIs will have access to the final pilot dataset for the purpose of characterizing the participant sample, characterizing the activity within the MOST+ system, and testing the study hypotheses. The study RAs will also have access to the dataset for the purpose of data entry and management. Expert moderators and eheadspace clinicians working within MOST+ will have access to individual and aggregated usage data available within the moderator interface.

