### Data Analysis

Frequency, duration, and patterns of use of MOST+ will be tracked in real time. Up-to-date charts will be visible on demand to MOST+ staff via the moderator interface of the online platform. This data will be aggregated into simple descriptive statistics to characterize participants’ use of the intervention. In addition, overall rates of MOST+ participation and aggregated data from the user feedback questionnaire will be compared with the *a priori* acceptability and safety criteria to determine success of the pilot. Supplementary paired samples *t* tests will be conducted to assess pre- to postintervention changes to outcomes. System usage will be examined as a covariate.

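### The usage covariate partly measures time since baseline, because the follow-up date moves with how long a participant stays enrolled

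*Protocol article*

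**What the plan says.** - **Analysis.** Under Data Analysis, paired "tests will be conducted to assess pre- to postintervention changes to outcomes", and the next sentence reads "System usage will be examined as a covariate". The same section says that frequency, duration and patterns of use are tracked.
- **Design.** The Abstract says that the intervention "will be evaluated via an uncontrolled single-group study".
- **Follow-up date.** Under Data Collection and Management, "Follow-up assessment will occur approximately 4 days after initial account deactivation". For those who stay enrolled throughout, "follow-up will occur as soon as possible following conclusion of the pilot". Sample Size confirms that follow-up is fitted to the initial period of engagement.
- **Length of enrollment.** Under Duration of Access, participants decide weekly whether to renew, giving 1 to 8 weeks.
- **What counts as usage.** Under Outcomes, "Usage data will include the number of log-ins, steps completed, and contributions to Talk It Out", together with contributions to The Café.
- **Access level.** Under Participants, "the following exclusions will apply for access to the social networking component of the intervention". The reasons are acute self-harm risk, clinician judgement, and failure to confirm age and complete induction by telephone. Acute Risk adds that a participant may later be returned to partial access.

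**The concern.** Usage is observed after baseline, and the follow-up rule ties it to elapsed time. A participant who renews for several weeks has more opportunity to log in, complete Steps and post, and is also measured later. People register when they are seeking help, so some improvement with time alone is plausible. No untreated group shows how much. A coefficient for total usage then combines any effect of use with the passage of time, and if scores tend to improve, the error favours the intervention.

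Access level adds a smaller complication. Partial-access participants cannot contribute to The Café or Talk It Out, so that part of the usage measure depends partly on clinical risk.

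At stake is how the usage association is read for the ten self-report measures that Table 1 schedules at both time points. They share one follow-up date per participant, so the same distortion can recur in each.

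**Working it through.** The article gives no SD, renewal rate, retention rate or expected change, so there is no stated figure to reproduce. The sizes below rest on the assumptions named.

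**1. Range of follow-up times (from the article).** Days to follow-up ≈ 7 × weeks enrolled + 4.
- One week: 7 × 1 + 4 = 11 days.
- Eight weeks: 7 × 8 + 4 = 60 days. Participants who stay to the end are seen as soon as possible after the pilot, so this end is approximate.

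**2. Spurious slope when use does nothing.** Let W be weeks enrolled, U total usage, and k the improvement per week in SD units. If use has no effect, the expected change in outcome per SD of usage is

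k × SD(W) × corr(U, W).

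This is zero only if k is zero or usage is unrelated to weeks enrolled.

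**3. Numbers.** Assumptions: entry over weeks 0 to 3 of the 8-week pilot; 50% renew each week, which with truncation at the pilot's end gives SD(W) ≈ 1.30 weeks; corr(U, W) ≈ 0.53 (a simulation gave about 0.5 to 0.56); baseline/follow-up correlation 0.6; 125 followed up.
- SD of change = √(2 × (1 − 0.6)) = 0.894.
- Standard error of the slope per SD of usage ≈ 0.894 / √125 = 0.080.

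| k (SD/week) | Spurious slope | Slope / SE | Chance of p < 0.05 |
|---|---|---|---|
| 0.05 | 0.034 | 0.43 | 7% |
| 0.10 | 0.069 | 0.86 | 14% |
| 0.15 | 0.103 | 1.29 | 25% |

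A simulation on these assumptions gave 7 to 26%. At 30% weekly renewal SD(W) is about 0.78 and the formula gives 6 to 12%; the simulation gave 7 to 12%. Across the renewal and retention assumptions tried, the range is roughly 5 to 30%.

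**4. A second simulation, different assumptions.** Improvement levels off (30-day time constant), weekly non-renewal is 45%, and 150 of 250 (60%) are followed up. Change is regressed on log usage, with no true effect of use.

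| Total spontaneous improvement | Usage significant |
|---|---|
| 0 SD | 4.1% |
| 0.3 SD | 7.2% |
| 0.5 SD | 10.0% |
| 0.8 SD | 20.0% |

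When there is improvement, nearly all of these results favour use. At 0.8 SD the rate is 14.2% with 40% followed up and 24.1% with 80%. Baseline adjustment alone does not help (13.3% at 0.5 SD, 23.8% at 0.8 SD). Baseline plus follow-up time gives 5.2% and 4.8%.

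**5. Access level at entry (20% held at partial access, assumed).** The direction is not fixed.
- Gate alone, regression to the mean, no baseline adjustment: 11.2%, almost all making use look harmful. With baseline: 5.0%.
- Gate alone, slower recovery in gated users: 7.7% unadjusted (mostly harmful), 6.0% with baseline (mostly beneficial).
- Gate plus timing at 0.5 SD: 4.9 to 5.6% unadjusted, because the biases partly cancel; 11.2 to 12.6% with baseline alone, almost all favouring use. In the slower-recovery case (12.6%), baseline, time and access level together give 5.0%.

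**6. Return to partial access after baseline.** If 5, 10 or 20% of users lose posting access because they are worsening, the unadjusted rates are 8.0%, 17.0% and 34.2%, almost all favouring use. The simulation removed all of these users' posts, including any made before the change, so it probably overstates the effect. The adjustments in steps 4 and 5 were not tested against this mechanism.

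**The case against.** The fairest defence is that one sentence in a condensed article is being held to the standard of a full model. The article fixes no usage metric, model or list of adjusters, and a statistical analysis plan may supply them. The tests are labelled supplementary and no causal claim is made. That limits the consequence but does not remove the point. The follow-up rule and the usage covariate are both stated, and together they produce the confounding whichever cumulative usage count is chosen.

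Strictly, renewal sets the follow-up date, not log-ins or posts. That is right; the counts follow because they accumulate over enrolled weeks. The unadjusted timing-plus-gate result, close to the nominal 5%, is also a fair point, but it depends on two biases happening to offset each other.

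Four stronger readings are tempting, and the article does not support them:
- **The method cannot be run because a paired t test takes no covariate.** The covariate is mentioned in a separate sentence and is not said to sit inside the t test.
- **Low use marks high clinical risk.** Restriction blocks social-network activity only; Web chat and the therapy content stay open, so log-ins and Steps can still accrue. Failed telephone contact also restricts access, so the partial-access group is mixed.
- **Use after the outcome was measured will be counted.** "Participants will be able to reactivate an expired account at any time during the study intervention period", but this is treated as a second episode of care, and nothing says that its usage is set against the first follow-up score.
- **The coefficient will serve as dose-response evidence for a randomised trial.** The Discussion bases progression on feasibility, acceptability and safety.

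**Conclusion.** The concern holds for timing. By the article's own rules, time to follow-up rises with weeks enrolled, so total usage partly measures time since baseline, and without a control group nothing else separates the two. Timing alone gives roughly 5 to 30% false-positive usage findings under assumed improvement of 0.05 to 0.15 SD per week, depending on assumed renewal and retention. If there is no improvement with time, there is no inflation from this source.

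Access level is a secondary confounder, limited to Café and Talk It Out posts. Its direction at entry is uncertain, and it can change later on signs of acute risk.

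Only the interpretation of the supplementary secondary outcomes is affected. The feasibility, acceptability and safety assessments do not use this coefficient.

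**What to change.** Replace the covariate sentence in Data Analysis with wording to this effect:

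1. Report mean pre-post change for each outcome from an analysis without usage.
2. Examine usage in a separate regression of the follow-up score on baseline score, days from registration to follow-up, initial access level, and usage intensity (for example per enrolled week), counted only up to the follow-up date. Define initial access level as the level granted by the initial screening, since everyone starts on partial access.
3. Report the usage coefficient as a non-causal association. Participants choose whether to renew and access can change with clinical state, so adjustment cannot turn it into an effect of dose.

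The cost is one paragraph and a few model terms. Usage is already tracked in real time and access level is already listed among the access data; the registration and follow-up dates need only be kept. The usage coefficient will be less precise and probably less favourable. Once follow-up time is in the model, duration of use cannot be separated from elapsed time. That limit comes from the design and should be stated.

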### Harms

System and privacy protection will be monitored by the study programmers. All attempts, both successful and unsuccessful, to log into the site are recorded in a database table that can be monitored. This table also informs a security mechanism whereby if five incorrect log-in attempts are made from the same internet protocol (IP) address within a 1-hour period, then an email alerting the development team is sent, and log-in access to the site is blocked for that IP address for the next hour. Online safety will be monitored proactively by the MOST+ clinicians, with supervision from the senior researchers. MOST+ clinicians will have the authority to respond to users’ reports of inappropriate material within the online platform and to automated email reports of posts that include potentially offending material. eheadspace staff will respond to indications of clinical risk according to the MOST+ safety algorithm (see Figure 1).

An important function of eheadspace and MOST+ is to facilitate support, containment, and appropriate referral wherever possible in instances of acute clinical risk. Successful implementation of the MOST+ clinical safety protocol will therefore be treated as appropriate use of the intervention and will not be automatically recorded as an adverse event. All activations of the safety protocol will nevertheless be recorded and reviewed by the coordinating investigators as part of ongoing monitoring of the feasibility and safety of the intervention. In addition, serious adverse events will be monitored, recorded, and reported to the study sponsor and ethics committee in accordance with Good Clinical Practice guidelines. Serious adverse events will be tracked throughout the duration of the study. Serious adverse events are defined as events that (1) Result in death, (2) Are life-threatening, (3) Require inpatient hospitalization or prolongation of existing hospitalization, (4) Result in persistent or significant disability or incapacity, or (5) Are other medically important events or reactions.

For each moderate to high-risk case, eheadspace documentation includes: (1) The facts of the case; (2) A clear opinion as to the level of risk; (3) A rationale for this opinion; (4) A statement of any consultations with carers and other involved agencies; and (5) Completion of a care plan. This reporting process will be followed by all eheadspace clinicians working within the MOST+ interface, and case notes involving activation of the MOST+ clinical safety protocol will be reviewed by the coordinating investigators.

In the event that clinical deterioration in a research participant is evident and attributable to usage of the MOST+ system, the relevant MOST+ clinician will communicate with the PIs. The investigators will subsequently inform the ethics committee. In addition, the coordinating investigators will inform the ethics committee in the unlikely event of a security breach of the online platform which compromises the privacy of participant information. The occurrence of either of these two events will be taken to indicate an unacceptable safety risk of the MOST+ system, as per the *a priori* intervention safety criteria.

## Results

Recruitment for the study commenced in October 2017. We expect to have initial results in March 2018, with more detailed qualitative and quantitative analyses to follow.

## Discussion

The aim of this project was to pilot test the next generation of eheadspace services. As such, MOST+ has been designed to harness the popularity and high demand of eheadspace by integrating a state-of-the-art online social media–based platform that weaves together attractive evidence-based, therapeutic content; peer moderation; peer-to-peer online social networking; and one-to-one online clinical support. This novel platform has the potential to deliver an enriched 24/7 youth-led therapeutic environment that caters for the needs of more young people and increases the overall scalability of clinical e-mental health services.

To date, we have developed and implemented the MOST model for individuals, in particular clinical groups, who are already in contact with mental health services [21,25]. The current research will provide valuable insights into the implementation of MOST on a platform accessible to young people whose characteristics, including location, access to face-to-face health services, and mental health concerns, may vary considerably. The flexibility required for MOST+ to be suitable and useful for individuals with a range of concerns is built into the platform. Specifically, the use of user-driven social networking and problem solving and therapy content that focuses on users’ positive traits and well-being are intended to ensure the intervention is widely applicable. Furthermore, with this flexible, online model of care, MOST+ could be implemented across cultural and geographic boundaries.

By investigating feasibility, acceptability, and safety, the data from this pilot will indicate the suitability of progressing to a large randomized controlled trial to assess the clinical effectiveness and cost-effectiveness of this model. In addition, feedback from users, super users, and clinicians will inform the development of future MOST+ interventions, allowing for improvements to both content and implementation. As a first step in providing nation-wide access to integrated user-directed psychosocial interventions, peer-moderated social networking, and clinician chat, this pilot study stands to advance clinical e-mental health services in Australia.

The final trial dataset will be retained by Orygen, The National Centre of Excellence in Youth Mental Health.

